# Study Summary

| **Title** | A randomized, controlled, partially double-blinded, Phase 3, Multi-center trial to determine if Curosurf® reduces the duration of mechanical ventilation in infants 24+0 to 31+6 weeks gestational age |
| --- | --- |
| **Short Title** | Curosurf study |
| **Protocol Number** | Curosurf-01 |
| **Phase** | Phase 3 |
| **Methodology** | Randomized, partially double-blinded study using a 1:1 randomization, of ventilated infants to receive either Curosurf® or BLES® by endotracheal method. |
| **Study Duration** | This study is expected to last 30 months, including time for analysis. |
| **Study Center(s)** | Multi-center, multiple sites in Canada |
| **Objectives** | The objective of the study is to determine whether the duration of ventilation in babies who receive Curosurf® is less than those who receive BLES® |
| **Number of Subjects** | The projected enrollment is 88 patients. Enrollment is competitive. |
| **Diagnosis and Main Inclusion Criteria** | Infants born between 24+0 and 31+6 weeks GA, admitted to the study centers NICU’s, with RDS, requiring intubation and surfactant therapy. |
| **Study Product, Dose, Route, Regimen** | Infants will be randomized in a 1:1 manner, to receive either the study drug, Curosurf® or the control drug, BLES®. The treatment dose for Curosurf® is 2.5 ml/kg (200mg/kg) for the first dose and 1.25 ml/kg (100mg/kg) for repeat doses. For BLES® the recommended dose is 5 ml/kg. Either drug is given by syringe into the endotracheal tube by a Respiratory Therapist. |
| **Duration of administration** | The study drug or control drug will be given once all inclusion and no exclusion criteria have been met. In the days to follow according to the status of the infant, repeated doses may be indicated. |
| **Reference therapy** | The control group will receive BLES®. This licensed medication is routinely used in both study centers for the treatment of ventilated infants with a diagnosis of RDS. |
| **Statistical Methodology** | Analysis of the primary outcome will use logistic regression, with the treatment group as the main independent variable, and adjusting for the stratification variables, centre and gestational age category. Secondary analyses will include comparison of mortality rates by treatment group using a similar logistic regression model. |

# Background Information and Scientific Rationale

## Background Information

Evidence for the efficacy of either prophylactic (within the first 30 minutes after birth regardless of respiratory status) or selective (when signs of respiratory distress syndrome or RDS are present) administration of surfactant comes from meta-analyses, which demonstrate a consistent 30-50% reduction in the odds of neonatal death and air leaks (1). As the increase in survival is mainly observed among extremely low birth weight (ELBW) infants, the incidence of bronchopulmonary dysplasia (BPD) - the chronic lung disease that follows ventilator and O2 therapy for RDS - has not been significantly reduced. BPD, defined by the need for supplemental O2 at 36 weeks post menstrual age (PMA), increases the risk of mortality and pulmonary and neurodevelopmental morbidity among ELBW infants (2). Recent large RCTs have demonstrated that early nasal continuous positive airway pressure (nCPAP) with selective surfactant therapy was as effective at reducing BPD or death as intubation and prophylactic surfactant (3-5).

Currently, the two surfactants available in Canada are BLES® (Bovine Lipid Extract Surfactant) purified from bovine lung lavage and beractant (Survanta) extracted from minced bovine lungs. Most neonatal intensive care units (NICUs) use BLES®, for its observed faster onset of action. The recommended dose is 5 ml/kg, the highest for an animal-derived surfactant. Recent observations of severe airway obstruction (SAO) with desaturation and/or bradycardia with BLES® were reported in a cohort of premature infants, with an incidence of SAO of 31% in ELBW infants (6).

In Europe and the USA, the most widely used surfactant is poractant alfa (Curosurf®), a surfactant extracted from porcine minced lungs. Compared to BLES® and Survanta, Curosurf® contains a higher concentration of phospholipids (27, 25, and 76 mg/ml respectively). This accounts for the dramatic improvement usually observed immediately after its administration, which translates into a higher rate of extubation success (7-9). The treatment dose is 2.5 ml/kg (200mg/kg) for the first dose and 1.25 ml/kg (100mg/kg) for repeat doses if indicated. A recent meta-analysis confirms that Curosurf®, compared to Survanta, leads to higher survival, shorter duration of mechanical ventilation, less re-dosing (needing > 1 dose of surfactant) and shorter admissions to NICU (10).

Current practice in Canada is to selectively intubate patients who demonstrate signs of RDS and provide them with BLES®, with the aim of extubating to nCPAP as soon as possible, in order to avoid or reduce lung injury. Despite our intent, the mean duration of intubation after surfactant for <30 weeks gestational age (GA) survivors in Ottawa was 6.8 days in 2010. In the same year, 60% of infants <30 weeks GA who received BLES® in Ottawa remained ventilated at 48 hours. Recent trials using Curosurf® report median durations of intubation of 2-5.5 days in infants <29 weeks GA as well as rates of BPD (21% in the CURPAP study) lower than the current incidence in Canada (44.8%) (7,8,11).

## Rationale

Recent studies in Europe and Australasia investigated the possibility of instilling surfactant directly in the trachea with a thin, soft tube under direct visualization, to avoid intubation and mechanical ventilation completely (11,12). These have shown feasibility and German investigators have reported very low rates of death or BPD (15%) in infants 26-28 weeks GA with that strategy (11). Discussions about adopting this approach are ongoing in Ontario and Canada but neonatologists are skeptical as to whether this would be possible using BLES®.

In Canada, our initial respiratory management changed in the last decade, however the surfactant used has remained unchanged since the late 1990’s. In the only published (abstract form only) RCT comparing BLES® to Exosurf, a synthetic surfactant no longer used in North America, no difference was found in the primary outcome (survival without BPD at 36 weeks PMA). As many secondary outcomes favored BLES®, the investigators concluded that BLES® was a superior surfactant (13). BLES® was compared to Survanta in only one small RCT. Patients who received BLES® achieved a faster clinical response in terms of oxygenation index. Mortality, ventilator days and chronic lung disease were not different between groups (14). There is no published study comparing BLES® to Curosurf®. This RCT will be the first clinical trial comparing Curosurf® to BLES® and the first use of Curosurf® in Canada. Introducing Curosurf® in Canada for the smallest of our infants might lead to changes in the approach to initial respiratory management translating to a better respiratory outcome.

## Potential Risks and Benefits

**Potential Benefits**

The potential benefit of this trial is that Curosurf® may reduce the time that the infant is exposed to mechanical ventilation, thereby potentially reducing the complications associated with intubation and ventilation, such as pneumonia and barovolutrauma. As well, Curosurf® is a more concentrated medication, therefore smaller volumes are administered. Infants may therefore have fewer complications (such as desaturations, apnea and bradycardia) due to airway obstruction in the period immediately following the administration.

**Potential Risks**

Administration of surfactant produces a transient decrease in ventilation (as surfactant partially occludes the airway) and oxygenation and may be associated with a pulmonary air leak (pneumothorax or pneumomediastinum) as compliance acutely improves. Pulmonary hemorrhage and intraventricular hemorrhages have been associated with surfactant administration as well. These risks are independent of the type of surfactant used.

For a detailed list of AEs associated with the study drugs please see the Drug Monographs (Appendices F and G). Please also note that many of the AEs listed for these drugs are in fact complications of prematurity but due to reporting regulations these AEs are listed in the drug AE section of the monographs.

# Study Objectives

The objective of the study is to compare the efficacy of the 2 surfactants Curosurf® and BLES®, at facilitating extubation and reducing pulmonary morbidities and also to compare the adverse events during surfactant administration in very premature infants. We hypothesize that, compared to BLES®, Curosurf® will increase the proportion of infants alive and extubated within 48 hours after surfactant therapy.

**Primary objective**

The primary objective of the study is to compare between the two groups, the number of subjects alive and extubated at 48 hours post surfactant administration.

**Secondary objectives**

To compare the duration of respiratory support, extubation failure rates, need for additional surfactant doses, adverse events (during and following administration), survival and pulmonary morbidities during hospital admission between the two groups.

# Eligibility Criteria

## Inclusion Criteria

- 1. Infants born between 24+0 and 31+6 weeks gestational age, admitted to the study centers
  2. Infants with RDS requiring intubation and surfactant therapy within 48 hours after birth

## Exclusion Criteria

- 1. Any infant more than 48 hours of age
  2. Any infant with a pulmonary hemorrhage
  3. Any infant with life-threatening congenital anomaly or one that is considered non-viable
  4. Any infant on rescue high frequency ventilation
  5. Any infant known to require early intubation and ventilation for surgical treatment of a congenital anomaly
  6. Any infant with anomalies of the upper or lower airway or mandible precluding use of nCPAP
  7. Any infant born after prolonged premature rupture of membranes (<22 weeks GA or >28 days prior to delivery)
  8. A parent/LAR who is incapable of, or unwilling, to give consent
  9. Participation in another clinical trial of any placebo, drug, biological, or device conducted under the provisions of a protocol
  10. Any other reason as deemed significant by the Investigator

# Study Design

## Description

This is a Phase 3 randomized, controlled, partially double-blinded trial. Infants with a diagnosis of RDS will be randomly assigned in a 1:1 manner to receive either the study drug, Curosurf® or BLES® (control group), by endotracheal method. A total of 88 infants will be in Canada. The study will take place at multiple sites. Enrollment is competitive.

Each infant enrolled into the study will receive a unique subject number. Subject codes will not be reused and each infant can be randomized only one time for the entire trial period.

The expected duration for each subject/infant is dependant on the gestational age of the infants at birth, as all babies will be followed until 36 weeks gestational age (GA) (or until discharge, which ever comes first), thus the longest duration for one infant should be 12 weeks.

Following the baseline and randomization time point there are a maximum of 6 assessment time points, starting at 30 minutes post study medication administration. The infants will be assessed by the Respiratory Therapist (RT) and the physician to determine whether or not they meet extubation criteria and can be extubated. Follow-up to collect information about the duration of ventilation will then occur at 2 weeks, 4 weeks and 8 weeks. The final time point for data collection is at 36 weeks gestational age or at discharge, whichever occurs first.

The entire trial should be completed within 30 months.

This will be a Regulated Trial and a Clinical Trial Application to Health Canada will be completed prior to beginning the trial. Local Research Ethics Board approval will be obtained at all sites, again prior to study start up.

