**Secondary Endpoints**

The following endpoints will also be measured in this study:

- duration of respiratory support (respiratory support via an endotracheal tube and non-invasive respiratory support)
- duration of NICU stay
- extubation failure rates
- need for additional surfactant doses
- adverse events (during and following administration of surfactant)
- death before discharge
- incidence of pulmonary morbidities up to 36 weeks GA

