# Expected Duration of Subject Participation

The duration for each infant in the study will vary according to the gestational age. Follow up is done until the infant is 36 weeks GA or at discharge, whichever is first. All assessments will be done according to the Timetable of Events. These time points are simply for data collection and no extra tests or procedures are done for the purposes of this study, from the perspective of the infant or the parent/LAR.

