## Discharge home or discharge from the NICU admitting unit

This time point can occur at 36 weeks gestation or before. All SAEs con meds, extubation failure and secondary outcome assessments data will be captured (if not previously done). Any SAE information will be gathered and completed, unless the SAE has not resolved.

| Timetable of Events | | | | | | | | | | | |
| --- | --- | --- | --- | --- | --- | --- | --- | --- | --- | --- | --- |
| **Evaluation** | **Baseline** | **30 m.**  **(± 15 min)** | **6 hrs**  **(± 30 min)** | **12 hrs**  **(± 2 hrs)** | **24 hrs**  **(± 2 hrs)** | **36 hrs**  **(± 2 hrs)** | **48 hrs**  **(± 2 hrs)** | **Week 2**  **(±1 week)** | **Week 4**  **(±1 week)** | **Week 8***  **(±1 week)** | **Discharge from hospital**  **(36 wksGA)** |
| Consent 1 | X |  |  |  |  |  |  |  |  |  |  |
| Medical/Medication History | X |  |  |  |  |  |  |  |  |  |  |
| Physical Exam 2 | X |  |  |  |  |  |  |  |  |  |  |
| Demographics | X |  |  |  |  |  |  |  |  |  |  |
| Randomization | X |  |  |  |  |  |  |  |  |  |  |
| Ventilator parameters3 | X | X | X | X | X | X | X |  |  |  |  |
| Con Meds | X |  |  |  |  |  | X | X | X | X | X |
| SAE assessment |  | X | X | X | X | X | X | X | X | X | X |
| Extubation failure assessment |  |  |  |  |  |  |  | X | X | X | X |
| Secondary outcome assessment |  |  |  |  |  |  |  |  |  |  | X |

1 Consent may be obtained from the mother antenatally or after the birth of the infant.

2 Includes weight, Temperature (Axillary), heart rate (apical), respirations.

3 Includes Rate, PL-LP, PEEP, Pressure support, FiO2, Mean, Tidal volume, IT, and Flow

***** Data collection at this time point is not done if the infant has already been discharged.

.

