# Appendix D: Secondary Outcomes

1. Extubation failure (defined as in Appendix C )

2. Duration of first intubation (in hours/days)

3. Total duration of respiratory support (ventilator and nCPAP) and

Total number of days of oxygen requirement

4. Number of doses of surfactant received

5. Adverse events during or after administration of surfactant:

a) Severe airway obstruction, defined as sudden and severe desaturation < 80% with bradycardia (heart rate <100 bpm) with absence of visualization of chest movements with no response to increases in ventilator pressure or bagging for ≥3 minutes and requiring suctioning of surfactant or change of endotracheal tube (ETT)

b) Need for cardiopulmonary resuscitation

c) Pulmonary hemorrhage, defined as fresh blood in the ETT lumen associated with an increase in ventilation or oxygen requirements

d) Pulmonary air leaks (pneumothorax and/or pulmonary interstitial emphysema (PIE) on CXR)

6. Bronchopulmonary dysplasia, defined as oxygen or respiratory support requirement at 36 weeks corrected GA

7. Mortality prior to discharge

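### Ending data collection at the earlier of 36 weeks and discharge contradicts three secondary endpoints: death before discharge, NICU stay, and 36-week BPD in infants sent home early

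*Protocol*

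**What the plan says.** The stopping rule for data collection is in Protocol section 4.1: "The final time point for data collection is at 36 weeks gestational age or at discharge, whichever occurs first". Section 5 restates it: "Follow up is done until the infant is 36 weeks GA or at discharge, whichever is first". Section 4.1 also draws the consequence: "thus the longest duration for one infant should be 12 weeks". Section 7.5, whose heading covers both going home and leaving the admitting NICU, adds: "This time point can occur at 36 weeks gestation or before". The Timetable of Events gives its last column a hospital-discharge label with 36 weeks in brackets, and that column holds the only mark for the secondary outcome assessment.

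The secondary endpoints in section 4.2 include "death before discharge" and "duration of NICU stay". Appendix D repeats mortality up to discharge, lists total respiratory support and total oxygen days without a cap at 36 weeks, and defines "Bronchopulmonary dysplasia, defined as oxygen or respiratory support requirement at 36 weeks corrected GA". Section 8.2 assigns mortality and oxygen use at 36 weeks to logistic regression, and ventilation and oxygen durations to Cox regression. The only censoring it mentions is death while ventilated.

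Section 7.4 tells sites to make every effort to keep following infants transferred to another institution.

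**The concern.** Each of these endpoints fixes its own observation period, and the stopping rule fixes a different one. Followed exactly, the rule has three effects.

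- **Death before discharge.** A death after 36 weeks in an infant who never left hospital falls outside scheduled collection. What gets analysed is death by the earlier of 36 weeks and discharge, under another name.
- **NICU stay.** For an infant still in the NICU at 36 weeks, the recorded stay depends only on gestational age at birth. Any treatment difference that shows after 36 weeks is invisible.
- **BPD.** An infant sent home before 36 weeks has no observation at the age on which the definition rests. Dropping such infants, counting them as free of BPD, or carrying forward their status at discharge gives different denominators and rates. If one surfactant led to earlier discharge, dropping them would remove more infants from that group.

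The secondary objective covers survival and pulmonary morbidity during the hospital admission, so these are named aims of the trial. An analysis plan can choose a method, but it cannot recover dates and outcomes that were never collected.

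**Working it through.** **Inputs.** Gestational age at birth is from section 3: "Infants born between 24+0 and 31+6 weeks gestational age, admitted to the study centers". The end of collection is the earlier of 36+0 weeks and discharge (sections 4.1 and 5). The stated maximum participation is 12 weeks (section 4.1).

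**1. Reproduce the protocol's own figure.** Longest follow-up = 36+0 minus 24+0 = 252 − 168 = 84 days = 12.0 weeks. This matches exactly, so the earlier-of-two-dates reading is the intended one and not a slip of wording.

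**2. Cap on recordable stay.** Cap in days = 252 − gestational age at birth in days.

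| Birth | Age in days | Cap |
|---|---|---|
| 24+0 | 168 | 84 |
| 27+0 | 189 | 63 |
| 31+6 | 223 | 29 |

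**3. What is lost beyond 36 weeks.** An infant who stays k weeks past 36+0 loses 7k days of stay, whatever the gestational age at birth. The discharge ages below are assumptions, because the protocol gives none. For birth at 24+0:

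| Assumed discharge (weeks) | True stay (days) | Recorded at most | Lost |
|---|---|---|---|
| 37 | 91 | 84 | 7 |
| 38 | 98 | 84 | 14 |
| 40 | 112 | 84 | 28 |
| 42 | 126 | 84 | 42 |

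**4. Endpoint against window.**

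| Endpoint | Needs | Available under the rule |
|---|---|---|
| Death before discharge | Vital status to discharge | Complete only if discharge is by 36 weeks |
| NICU stay | NICU discharge date | Complete only if the infant leaves the NICU by 36 weeks |
| BPD, oxygen at 36 weeks | Status at 36 weeks | Complete only if still under follow-up at 36 weeks |
| Ventilation and oxygen durations | End date, or a censoring date | Censored at 36 weeks |

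**5. Could another visit fill the gap?** Week 8 falls after 36+0 for any infant born after 28+0, since 28+0 plus 8 weeks is 36+0. The timetable omits it only after discharge. This implies some collection past 36 weeks, which itself disagrees with sections 4.1 and 5. It does not help here, because only concomitant medications, SAEs and extubation failure are marked at that visit.

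**6. Could SAE reporting catch late deaths?** Section 7.4 refers to a 30-day SAE follow-up, and the timetable has no SAE assessment after the final visit. SAEs already open are followed further, but capture of a new late death is not assured.

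**7. Transferred infants.** Section 7.4 says to follow them. The heading of section 7.5 makes leaving the admitting NICU a final visit. The timetable label says hospital discharge. The three do not agree on which discharge ends collection.

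**The case against.** The strongest reply is that this touches secondary endpoints only. The primary endpoint is settled at 48 hours and the sample size of 44 per group rests on it alone. That stands, and it limits the severity.

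A reader might infer that respiratory-support and oxygen days are lost as well. The documents do not support that. Section 8.2 uses Cox regression for ventilation and oxygen, and an infant still on support at 36 weeks can be right-censored. Naming death on ventilation as censoring does not exclude censoring at the end of follow-up, a detail that an analysis plan may hold. Section 8.2 names no method for NICU stay or for total respiratory support, so the defence is incomplete for those two.

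A reader might also infer that transferred infants have no 36-week status. Section 7.4 and the timetable label point the other way; only the heading of section 7.5 suggests it. That is a conflict to reconcile, not an established loss.

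Nor does it follow that the secondary objective on pulmonary morbidity is unanswerable. Section 4.2 limits those morbidities to 36 weeks, and for infants still in hospital BPD is observed exactly on time. For infants sent home earlier, status at discharge would be on record and a plain classification rule might suffice, but the protocol states none.

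Finally, one might put a count on the infants affected. Any such count would rest on assumed discharge rates, so none is given here.

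**Conclusion.** The contradiction is real and lies within the protocol. It is firm for death before discharge and NICU stay in infants who remain past 36 weeks, and for 36-week oxygen and BPD status in infants sent home earlier. For transferred infants it is an inconsistency between sections 7.4, 7.5 and the timetable.

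Its size can be given only as caps on recordable stay: 84, 63 and 29 days for birth at 24+0, 27+0 and 31+6. These follow from the rule without further assumption. The number of infants beyond the cap or discharged before 36 weeks cannot be derived from the documents.

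The conclusion assumes that sites apply the rule as written; a site that charts to discharge anyway would lose less. The primary result is not at risk. This should be fixed, because data not collected cannot be restored at the analysis stage.

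**What to change.** Amend sections 4.1, 5 and 7.5, and align section 4.2, Appendix D and the timetable, in one of two ways.

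- **(a) Collect what the endpoints need.** From charts, record vital status and the dates of NICU and hospital discharge at final discharge. Record oxygen and respiratory-support status at 36 weeks for every survivor, wherever the infant then is. The 12-week maximum in section 4.1 must then be revised. Cost: a few chart fields and some contact with receiving hospitals or families. No tests on infants are added.
- **(b) Keep the 36-week horizon.** Rename the endpoints as death by 36 weeks and as NICU, support and oxygen days to 36 weeks, with censoring at 36 weeks. State how infants discharged earlier are classified for BPD. Cost: wording only, but narrower endpoints that say nothing about outcomes after 36 weeks.

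Under either option, state whether discharge means from the admitting NICU or from hospital, reconcile that with the instruction to follow transferred infants, and say whether Week 8 applies after 36 weeks.
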